# Protocol: evaluation of an optimised couples-focused intervention to increase testing for HIV in rural KwaZulu-Natal, South Africa, the Igugu Lethu (‘Our treasure’) cohort study

**DOI:** 10.1186/s12889-022-13894-3

**Published:** 2022-08-19

**Keywords:** Couples HIV testing and counselling, Couples-focused intervention, Behavioural intervention, Couples health, South Africa

## Abstract

**Background:**

Between 2012 and 2015, the Uthando Lwethu (UL) study demonstrated that a theory-based behavioural couples-focused intervention significantly increased participation in couples HIV testing and counselling (CHTC) among South African couples who had never previously tested for HIV together or mutually disclosed their HIV status, 42% compared to 12% of the control group at 9 months follow-up. Although effective, we were nonetheless concerned that in this high prevalence setting the majority (58%) of intervention couples chose not to test together. In response we optimised the UL intervention and in a new study, ‘Igugu Lethu’, we are evaluating the success of the optimised intervention in promoting CHTC.

**Methods:**

One hundred eighty heterosexual couples, who have been in a relationship together for at least 6 months, are being recruited and offered the optimised couples-focused intervention. In the Igugu Lethu study, we have expanded the health screening visit offered to couples to include other health conditions in addition to CHTC. Enrolled couples who choose to schedule CHTC will also have the opportunity to undertake a random blood glucose test, blood pressure and BMI measurements, and self-sample for STI testing as part of their health screening. Individual surveys are administered at baseline, 4 weeks and 4 months follow-up. The proportion of couples who decide to test together for HIV will be compared to the results of the intervention arm in the UL study (historical controls). To facilitate this comparison, we will use the same recruitment and follow-up strategies in the same community as the previous UL study.

**Discussion:**

By strengthening communication and functioning within the relationship, the Igugu Lethu study, like the previous UL study, aims to transform the motivation of individual partners from a focus on their own health to shared health as a couple. The Igugu Lethu study findings will answer whether the optimised couples-focused behavioural intervention and offering CHTC as part of a broader health screening for couples can increase uptake of CHTC by 40%, an outcome that would be highly desirable in populations with high HIV prevalence.

**Trial registration:**

Retrospectively registered. ISRCTN Registry ISRCTN 46162564 Registered on 26th May 2022.

**Supplementary Information:**

The online version contains supplementary material available at 10.1186/s12889-022-13894-3.

## Background

South Africa has experienced one of the world’s most severe generalised HIV epidemics. In 2011, HIV prevalence was 29% among resident adults aged 15–49 years in KwaZulu-Natal (KZN) [1]. Between 2004 and 2011 HIV incidence in KZN was 2.63 per 100 person-years (95% CI 2.50 to 2.77) [2], with the majority of new infections occurring within heterosexual partnerships. Current recommendations are that HIV treatment should be started as soon as diagnosis is made [3]. Therefore, regular HIV testing remains crucial to achieving high levels of treatment coverage and the gateway for treatment and prevention pathways (e.g. pre-exposure prophylaxis). South African HIV testing campaigns have increased individual knowledge of HIV status but have not overcome barriers to repeat HIV testing and disclosure of HIV status to sexual partners [4]. Gender-specific concerns about HIV testing and treatment are well documented [5]. Thus, it is important that universal test and treat and treatment as prevention efforts are sensitive to men and women’s relationships with partners and family. In couples HIV testing and counselling (CHTC), couples are counselled, tested and receive their HIV results together [6]. In South Africa, as elsewhere in sub-Saharan Africa, the provision and uptake of CHTC remains low [7]. CHTC accomplishes two important goals. First, knowledge of each other’s HIV status can facilitate risk-reduction behaviour within partnerships via effecting positive changes (e.g., condom use) in sexual behaviour with primary and any concurrent partners. Second, knowledge of HIV status can increase access to treatment and care for HIV-positive individuals, as well as reinforce behavioural choices (e.g., limiting concurrent partners) to stay HIV-negative.

Between 2012 and 2015, the Uthando Lwethu Study tested the efficacy of an interdependence theory-based behavioural couples-focused intervention to increase participation in CHTC in South Africa among couples who had never tested for HIV together or mutually disclosed their HIV status [8]. Three hundred thirty-two couples were randomised to the intervention arm (168 couples) or the control arm (164 couples). The intervention arm received two group sessions and four couples counselling sessions, focused on problem-solving and communication skills and was highly effective in increasing the proportion of couples that decided to test for HIV together within 9 months after enrolment, (42% v. 12% [*p* < 0.001]) compared to the control group [9]. Concerned that, in a high HIV prevalence and continued HIV incidence setting [10], 58% of intervention couples did not choose to test together during the Uthando Lwethu study, we optimised the Uthando Lwethu intervention using the Person-Based Approach to intervention development and optimisation [11]. The details of the process of optimising the intervention have been published elsewhere [12]. In brief, a qualitative study was conducted with 20 purposively sampled couples who were formerly enrolled in the intervention arm of the Uthando Lwethu Study, and with 5 study staff who delivered intervention components, with the aim of exploring experiences of the intervention and barriers to testing. The past participants sampled included couples who did not attend couples counselling sessions and did not test for HIV together, some couples who attended all couples counselling sessions and tested for HIV together during follow-up, and others who only took up part of the intervention, with or without deciding to test for HIV together. Developing guiding principles and a logic model that showed how the optimised intervention would increase uptake to CHTC ensured that optimisations were grounded in the local context and drew on theoretical constructs [12]. The optimised intervention still involves two group sessions and up to four couples’ counselling sessions but differs from the Uthando Lwethu intervention in session content, involving community members speaking publicly about their HIV testing history and HIV status, and the possibility that the number of counselling sessions provided will be less if the couple engages in couples HIV testing at an earlier point in the intervention.

In South Africa, rates of intimate partner violence (IPV) reported in the literature are high [13]. The most recent Demographic Health Survey in South Africa (2016) reports one in four (26%) ever-partnered women age 18 or older have experienced physical, sexual, or emotional violence committed by a partner in their lifetime [14]. In the Uthando Lwethu study, among the 448 couples screened for eligibility, there were almost no reports of a history of IPV, and no reports of IPV during study follow-up were recorded. The Uthando Lwethu study excluded couples with a recent history of IPV (within last 6 months) because it was recognised that such couples would need both a different intervention and, support by staff with specific training and experience of counselling couples experiencing ongoing IPV. However, the Uthando Lwethu study included participants where an experience of IPV had occurred less recently. Thus, minimising selective exclusion of people at a high risk of HIV-infection.

To normalise HIV testing in research studies, in recent years HIV testing is increasingly offered as part of a broader health check [15–17], which led us to include screening for other conditions as part of our CHTC offer during follow-up, and to promote this as an opportunity for ‘couples health screening’.

### Study setting

As was the Uthando Lwethu study [8, 9], the Igugu Lethu study will be conducted at Human Sciences Research Council’s (HSRC) Sweetwaters research site in the rural Sweetwaters community west of the capital of KwaZulu-Natal, Pietermaritzburg (Fig. 1, created by [name] [18]). Part of the Greater Edendale Area, the community of around 600,000 people, is representative of the many Zulu communities in the province. The Sweetwaters community experiences high rates of infectious diseases such as HIV and TB, as well as non-communicable disease [19, 20]. The only healthcare options available to most Sweetwaters community members are free district clinics run by the provincial Department of Health and dispersed mobile clinic providers operated by NGOs; private health clinics are not an option for the majority of community members, given the low employment rate and low median monthly household income.

**Fig. 1 Fig1:**
[figure not shown]
Study location, Pietermaritzburg, KwaZulu-Natal, South Africa. Compiled from data provided by Stats SA, Community Profiles 2011 dataset [18]

In terms of non-communicable diseases (NCDs), adult diabetes is now a major problem in some countries in sub-Saharan Africa [21]. In the next decade adult diabetes is anticipated to become one of the most challenging public health conditions throughout the region, partly due to effective HIV treatment extending life expectancy, as well as changes in diets and lifestyles [22]. The age-standardised prevalence of diabetes in South Africans aged 15+ was 10.1% in 2011, 90–95% of which is type 2 diabetes [23]. The high prevalence of diabetes complications and mortality in adults with diabetes typically results from poor glycaemic control [22]. In South Africa, diabetes was the second largest underlying cause of death among adults aged 15–44 years in 2015 [24]. South Africa’s Strategic Plan for the Prevention and Control of Non-Communicable Diseases 2013–17 strategy [25] set a target of a 30% increase in the percentage of diabetic patients who are well controlled by 2020.

Obesity and hypertension are recognised as leading risk factors for cardiac diseases in low- and middle-income countries. In rural KwaZulu-Natal (KZN), population-based studies have reported the measured prevalence of obesity (BMI > 30 kg/m2) and hypertension (systolic or diastolic blood pressure > 140 or 90 mmHg, respectively) at 32 and 24% respectively among adults aged 15–50 years in 2004 [26]. Other population studies in KZN have documented similar levels of obesity and hypertension and documented pronounced gender differences, with 6.5 times higher prevalence of obesity in women and 1.4 times higher prevalence of hypertension in women than in men [19, 27]. The dual epidemics of communicable and non-communicable diseases in sub-Saharan Africa mean that many adults are living with more than one diagnosis, often managing co-morbidities alongside HIV. In a study of adults attending a primary care clinic in Khayelitsha, Western Cape, South Africa, in 2013 with at least one chronic illness (HIV, tuberculosis, diabetes, and hypertension), hypertension was the most common morbidity (65%), and 22.6% of patients had multimorbidity, with an increasing prevalence with age [28].

The four curable sexually transmitted infections (STIs, chlamydia, gonorrhoea, syphilis, and trichomoniasis) are prevalent in KZN, with significant sexual and reproductive health consequences including genital symptoms, pregnancy complications, infertility, and enhanced HIV transmission [29]. The standard of care for STIs in sub-Saharan Africa is syndromic management i.e. presumptive treatment without confirmatory laboratory tests [30]. The importance of partner notification and treatment is emphasised in STI clinical care but the strategy is passive. Offering lab STI-testing to couples provides opportunities to treat asymptomatic cases, facilitate partner treatment and, promote reproductive health, and fits well with the aims of South Africa’s National Strategic Plan on HIV, TB and STIs (2017–2022) [31].

At the Sweetwaters site, it is standard protocol to register all individuals who interact with a research study by fingerprint scanning to avoid multiple screening or enrolment of the same person. This biometric approach has been successfully implemented in several studies [17, 32, 33].

## Methods / design

The current protocol is version 1.3 dated 3rd November 2020. All protocol modifications will be communicated to the Human Sciences Research Council and the University of Southampton Ethics Committees for approval before they are implemented.

### Study objectives

The primary objective of the Igugu Lethu study is to measure the efficacy of our optimised theory-based and culturally appropriate couples-focused intervention on the uptake of HIV testing as a couple. We also have four secondary objectives. First, we aim to investigate the extent to which relationship dynamics are factors in achieving the outcome of couples’ uptake of HIV testing together. Second, we aim to explore whether couples take up other testing opportunities offered during the health screening visit, and the frequency of couples’ health concordance (the same status) for the different tests conducted. Third, we aim to identify operational reasons for failure or success in implementing the intervention and of the study as a whole. Finally, we aim to explore the penile microbiome functional characteristics of male partners and the vaginal microbiome functional characteristics of female partners and concordance in these characteristics within couples.

### Study design

Igugu Lethu is a prospective cohort study. Figure 2 summarises the study flow, including two stages of recruitment (initial screening and baseline screening) to determine the eligibility of couples to participate in the Igugu Lethu study, and the intervention sessions and follow-up assessments for those enrolled.

**Fig. 2 Fig2:**
[figure not shown]
Study flow

To maintain comparability with the Uthando Lwethu study, we will use the same eligibility criteria and similar recruitment and follow-up strategies used in the Uthando Lwethu study, with some adjustments for SARS-CoV-2 risk mitigation.

### Eligibility criteria

#### Inclusion criteria

Couples are considered eligible for baseline screening if they meet these inclusion criteria:Both partners 18 years and olderIn a primary relationship with an opposite sex partner. [Defined as: “Are you currently in a relationship with a person of the opposite sex to whom you feel committed above anyone else and with whom you have had sexual relations”]Both partners report the relationship length has lasted at least 6 monthsBoth partners are willing and able to provide informed consent

#### Exclusion criteria

Couples are considered ineligible for baseline screening if they meet these exclusion criteria:Both partners report participating in couples-focused testing for HIV with their current partner [Defined as: Both partners tested for HIV at the same time and disclosed the results].Either partner reports their current marital status as polygamous.Either partner reports participating in the Uthando Lwethu studyEither partner fails to answer exploratory relationship-focused questions about their partner.

As in the Uthando Lwethu study, couples who complete baseline screening will be considered ineligible to participate if either of the following additional exclusion criteria is determined to have been met:Either partner reports intimate partner violence (as actor or recipient) within the past 6 months with their current partnerBoth partners have ever disclosed HIV test results to each other [via individual or couples testing].

### Recruitment

#### Initial screening

To identify potential participants for initial screening, ward leaders, community working group members, and other contacts in the target community will circulate our study advert using WhatsApp, text etc. Interested potential participants are asked to contact the study team via the contact details included in the advert. The study will also be promoted by including the study advert in the local newspapers and on local radio, and by the HSRC community outreach team as they attend meetings and events in the community and in public areas in the community, such as markets, churches, workplaces, bus and taxi stands, and community centres using a loudhailer. If a couple or an individual is interested in participating in the study, recruiters will determine their eligibility through an initial screening survey over the phone. Recruiters will emphasise that both partners must complete the initial screening to determine if the couple is eligible for the baseline screening.

#### Baseline screening

Once both partners have completed the initial screening and if they are both eligible, a staff member will contact them to schedule a baseline screening visit. Experience during the Uthando Lwethu study showed that some couples who attended a screening visit were pretending to be couples in order to obtain the reimbursement. To discourage pretend couples, at the beginning of the baseline screening appointment, the couple will be individually asked questions of each partner to check if each partner knows the other (without recording the answers). The baseline screening continues only for couples where answers given by both partners are consistent.

Once couples have given informed consent, each partner will be asked to register with fingerprint scanning, and then a baseline survey will be administered, which takes approximately 60 min to complete. If either partner’s score suggests severe violence has occurred within the relationship in the last 6 months or both partners report HIV disclosure to each other, the couple will be ineligible to continue the study. If neither partner reports severe domestic violence in the relationship, and a maximum of one partner reports HIV disclosure, the couple is eligible to continue the Igugu Lethu study.

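### The Exclusion criteria bar couples reporting any intimate partner violence in the past 6 months, but Baseline screening bars only severe violence and admits the rest

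*Protocol article*

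**What the plan says.** Two sections of the protocol article set the violence exclusion that is decided from the baseline survey.

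- **Exclusion criteria.** Among the additional criteria applied after baseline screening, a couple is ineligible if "Either partner reports intimate partner violence (as actor or recipient) within the past 6 months" with the current partner. No severity threshold is given, and the list is presented as matching Uthando Lwethu.
- **Baseline screening.** A couple is ineligible if either partner's "score suggests severe violence has occurred within the relationship in the last 6 months", or if both partners report disclosing HIV results to each other. The next sentence gives the converse: "If neither partner reports severe domestic violence in the relationship, and a maximum of one partner reports HIV disclosure, the couple is eligible to continue".

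Three other places bear on the point.

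- **Background.** It describes the Uthando Lwethu exclusion as recent IPV, within 6 months, with no mention of severity. The reason given is that such couples would need another kind of intervention and counsellors trained for it. Couples whose violence was less recent were included.
- **Study design (under Figure 2).** To keep the cohorts comparable, "we will use the same eligibility criteria and similar recruitment and follow-up strategies used in the Uthando Lwethu study".
- **Baseline survey.** Domestic violence measures are used to confirm eligibility, and all measures are said to come from Uthando Lwethu. No score or cut-off is stated.

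**The concern.** The two sections govern one decision, made at one visit from one survey, yet they give different answers for some couples. Two things depend on which answer staff use.

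The first is participant protection. The Background justifies the exclusion by saying that couples with recent violence need support this intervention is not built to give. The only relaxation it describes is by time since the violence, not by severity. Under the Baseline screening wording, some couples with recent violence would be enrolled.

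The second is the historical comparison. The primary outcome sets uptake in this cohort against uptake in the Uthando Lwethu intervention arm, so the claim of identical eligibility is part of the design. If the two studies applied different violence rules, that claim would be wrong for this criterion.

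**Working it through.** The check is mainly a comparison of the sections. The table takes each kind of couple through the wordings, assuming every other criterion is met and at most one partner reports HIV disclosure.

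| Violence reported with current partner | Exclusion criteria | Baseline screening, ineligibility sentence | Baseline screening, eligibility sentence |
|---|---|---|---|
| None | Not excluded | Not excluded | Eligible |
| Non-severe, past 6 months | **Excluded** | **Not excluded** | **Eligible** |
| Severe, past 6 months | Excluded | Excluded | Condition not met |
| Non-severe, longer ago only | Not excluded | Not excluded | Eligible |
| Severe, longer ago only | Not excluded | **Not excluded** | **Condition not met** |

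The table shows two conflicts.

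1. *Severity (row 2).* The sections contradict each other outright. Baseline screening states the severity condition in both directions: severe means ineligible, not severe means eligible. It therefore cannot be read as shorthand for the broader criterion, because it positively admits couples whom the Exclusion criteria bar.
2. *Time window (row 5).* The eligibility sentence omits the 6 months. A couple with severe violence only in the more distant past is not made ineligible by the first sentence, but does not meet the condition in the second. The Background says couples with less recent violence were included in the earlier study.

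Nothing in the Baseline survey section resolves either conflict, since it gives no cut-off that would make the two wordings equivalent.

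**Does the sample-size figure depend on this?** Inputs from the Sample size section:

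- 65/168 = 38.7% of historical couples tested together by 4 months.
- The target is 55%.
- 180 × 0.95 = 171 couples remain after 5% loss.
- The test is at the 5% level, taken as two-sided.

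The formula is power = Φ[(|p2 − p1| − 1.96·SE0)/SE1], where SE0 is the pooled and SE1 the unpooled standard error.

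- Pooled proportion: (65 + 0.55 × 171)/339 = 0.469.
- SE0 = √[0.469 × 0.531 × (1/168 + 1/171)] = 0.0542.
- SE1 = √[0.387 × 0.613/168 + 0.55 × 0.45/171] = 0.0535.
- Power = Φ[(0.163 − 0.106)/0.0535] = 85.6%.

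The stated figure of more than 85% is reproduced. With the control rate rounded to 39%, power is 84.2%. No input refers to the violence rule, so the contradiction leaves the sample-size calculation untouched.

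**How many couples fall in row 2?** The article gives no frequency of recent non-severe violence. Its only figure from an earlier screening of this kind is the near absence of reported IPV history among 448 couples screened for Uthando Lwethu, with none recorded during follow-up. The 26% in the Background is a national figure for lifetime experience of physical, sexual or emotional violence among women, and does not measure this group.

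**The case against.** The best defence is that the Exclusion criteria summarise a rule which Baseline screening puts into practice as a score. Since the measures were all used in Uthando Lwethu, both studies may have applied the same cut-off, so that the cohorts match and only the wording is loose. This cannot be ruled out. It does limit the point: a mismatch with the historical controls is possible but not shown. It does not remove the contradiction, because the article states two rules that cannot both be followed for a couple reporting recent non-severe violence.

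A second defence is that safeguards exist. Baseline characteristics will be compared with Uthando Lwethu, with adjustment by logistic regression if they differ substantially. Staff are trained on coercion and partner violence, referral routes are in place, and safety is monitored routinely. All of this stands. Two limits remain. Regression has little to work with if one cohort excluded such couples altogether, and staff training does not tell a screener which couples to enrol.

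A reader might infer something stronger: that the primary comparison is materially biased. The documents do not support that.

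- No section links non-severe violence to uptake of couples testing.
- A sizeable effect needs a sizeable group. If, purely as an assumption, 10% of couples fell between the rules and their uptake were 39% instead of 55%, overall uptake would be 0.90 × 55% + 0.10 × 39% = 53.4%. At an assumed 2% it would be 54.7%.
- A 10% share would correspond to about 45 of the 448 couples screened earlier (0.10 × 448), which is hard to square with almost no reports of IPV.

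A reader might also infer that Uthando Lwethu applied the broader rule, since the Background and the Exclusion criteria both describe it without a severity threshold. Neither section shows how violence was scored in practice, so this too is unproven.

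**Conclusion.** The point holds as an internal contradiction in an eligibility rule. Couples reporting non-severe violence in the past 6 months are excluded under one section and eligible under the other, and the eligibility sentence in Baseline screening also loses the time window. It needs correcting because the exclusion protects couples whom the article itself says need different support, and because it sits beneath the claim of identical eligibility to the historical controls.

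Its size is unknown and may be small; if almost no couples report recent violence, the effect on the primary result is negligible. The conclusion rests only on the wording of the two sections. It assumes nothing about which rule staff applied, which rule the earlier study applied, or any link between violence and testing.

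**What to change.** 1. Reconcile the Exclusion criteria and Baseline screening sections, on both severity and time window, with each other and with the rule Uthando Lwethu actually applied, and word them alike. Which rule is right is for the investigators to establish, not for this review.
2. State which rule staff have used since recruitment began in December 2020.
3. If that rule differs from the one used in Uthando Lwethu, and if the violence measures shared by the two surveys allow couples to be classified in the same way, add a sensitivity analysis of the primary comparison restricted, in both cohorts, to couples eligible under both wordings. The article mentions measures and a score but does not say whether item-level answers are held for either study, so feasibility must be confirmed first. If the rules prove to be the same, this analysis is not needed.

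The cost is one clarification, at most one extra analysis, and possibly a few fewer couples in that analysis.
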